## Abstract

**Background:**

Approximately 30% to 50% of patients who are referred for diagnostic coronary angiography are found to have no obstructive coronary artery disease (CAD). Ischemia and nonobstructive coronary arteries (INOCA) is increasingly recognized and encompasses coronary microvascular dysfunction, vasospastic angina, symptomatic myocardial bridging, and other vasomotor disorders. However, the prevalence of these disorders and whether underlying atherosclerotic plaque burden and morphology affect the long-term outcomes of each physiologic phenotype is unknown.

**Methods:**

The DISCOVER INOCA registry is ongoing at 8 centers in the United States and plans to enroll 500 patients with ischemic heart disease referred for angiography undergoing coronary function testing (CFT). All participants will complete patient-reported outcome measures and undergo protocol-guided angiography, acetylcholine provocation, coronary thermodilution, and intravascular imaging. Follow-up assessments occur at 30 days, 6 months, 1 year, and annually for 5 years. The primary short-term end point is the prevalence of INOCA phenotypes based on physiology and the degree of atherosclerosis based on intravascular ultrasound or optical coherence tomography (intravascular imaging). The primary long-term end point is the incidence of major adverse cardiovascular events, defined as a composite of cardiovascular death, myocardial infarction, hospitalization for cardiovascular causes, or coronary revascularization at a follow-up of 5 years. At the time of this publication, 100 participants have been enrolled.

**Conclusions:**

DISCOVER INOCA is the first prospective study of INOCA patients to integrate anatomic and physiologic measures of disease and correlate them with long-term outcomes. DISCOVER INOCA will report on the prevalence of INOCA phenotypes, the safety of comprehensive invasive CFT, and the impact of testing on diagnoses and medical therapy. Symptoms and cardiovascular adverse events at long-term follow-up will be determined in patients with no obstructive CAD undergoing angiography.

## Introduction

Among patients referred for invasive coronary angiography (ICA) with or without ischemia on noninvasive stress testing, nearly 50% are found to have no obstructive coronary artery disease (CAD).^1^, ^2^, ^3^ Myocardial ischemia and nonobstructive coronary arteries (INOCA) is an umbrella term encompassing specific syndromes including coronary microvascular dysfunction (CMD) due to structural abnormalities or abnormally elevated resting flow, vasospastic angina (VSA), diffuse physiologically significant epicardial CAD, endothelial dysfunction, and symptomatic myocardial bridging. Previous studies suggest that there are 3 to 4 million people in the United States who suffer from INOCA.^4^^,^^5^ Compared with patients with obstructive CAD, these patients are more likely to suffer from anxiety, depression, and recurrent symptoms.^6^ Furthermore, compared with healthy controls, these patients are at increased risk for major adverse cardiovascular events (MACE) and cardiovascular mortality.^7^^,^^8^

Invasive anatomic and physiologic assessment of patients with INOCA has revealed epicardial endothelial dysfunction, CMD, myocardial bridging, or diffuse epicardial atherosclerosis in >75% of patients.^2^ Recent studies have shown that angina and quality of life can be improved when coronary physiology assessment is incorporated into clinical care.^9^^,^^10^ However, comprehensive assessments of coronary physiology (including the epicardial vessels and microvascular bed) with coronary function testing (CFT) are currently not performed routinely in most medical centers despite being recommended by professional society guidelines.^6^^,^^11^^,^^12^ The rationale for performing intravascular imaging and comprehensive coronary physiology assessment in patients with INOCA is that ICA alone cannot diagnose or exclude CMD, diffuse atherosclerosis, physiologically significant myocardial bridging, endothelial dysfunction, or dynamic processes such as coronary vasospasm.^9^ Additionally, determining the specific INOCA physiologic phenotype can help guide medical therapy and long-term prognosis.^6^^,^^13^

This prospective, multicenter registry will enroll up to 500 patients presenting with symptomatic ischemic heart disease and referred for ICA based on clinical indications. The overall objective of the Determining the Cause of Coronary Vasomotor Disorders in Patients With Ischemia and Nonobstructive Coronary Arteries (DISCOVER INOCA) Registry is to characterize phenotypes of INOCA and long-term outcomes based on both an anatomic evaluation (ICA and intravascular imaging) and physiologic assessment with the CoroFlow Cardiovascular System (Abbott Vascular) (Central Illustration). In this study, we aim to: (1) describe the prevalence of the INOCA phenotypes: CMD, VSA, mixed CMD/VSA, myocardial bridging, and other disorders of coronary physiology; (2) characterize the burden of epicardial coronary artery atherosclerosis and myocardial bridging; and (3) characterize the natural history and outcomes of patients with INOCA and determine variables associated with MACE.

**Central Illustration fig3:**
[figure not shown]
The DISCOVER INOCA multicenter registry aims to identify specific phenotypes of ischemia and nonobstructive coronary arteries through combined anatomic and physiological assessments (CoroFlow Cardiovascular System) and determine long-term outcomes. MACE, major adverse cardiovascular events (composite of cardiovascular death, myocardial infarction, hospitalization for cardiovascular causes, or coronary revascularization).

## Methods

### Study design

DISCOVER INOCA is a prospective, multicenter registry of patients with INOCA evaluated by ICA, intravascular imaging, and physiologic assessment with the CoroFlow Cardiovascular System (Central Illustration). The study is registered at ClinicalTrials.gov (NCT05288361). Participants will be enrolled at up to 10 investigational sites in the United States with prior experience performing CFT. A current list of investigational sites is provided in Supplemental Table S1. Clinical end points will be adjudicated by independent physician review by a provider who is not part of the study team. The relationship of these events to the procedure and physiology assessment protocol will also be adjudicated. Index procedure angiographic data, physiologic assessments, and intracoronary imaging will be analyzed offline by an angiographic core laboratory and intravascular imaging core laboratory (Yale Cardiovascular Research Group).

### Screening process and eligibility criteria

Patients with suspected ischemic heart disease that are scheduled for clinically indicated cardiac catheterization at the recommendation of their physician will be screened for inclusion in the registry. Participants must speak English or Spanish as the primary language. Up to 500 eligible patients who meet all inclusion criteria (Table 1) and no exclusion criteria (Table 2) will be enrolled in the study. The point of enrollment is investigator certification at the completion of the index procedure cardiac catheterization that all eligibility criteria are met. Participants will remain enrolled in the study regardless of the findings of the study procedure, including those with normal coronary physiology. The study flow diagram is presented in Figure 1. The following study measures must be assessed prior to the index procedure: Canadian Cardiovascular Society Anginal Classification, Seattle Angina Questionnaire, EuroQol 5 Dimensions – 5 Levels, Patient Health Questionnaire-8, and Generalized Anxiety Disorder-7, as well as preprocedure medications.

**Table 1 tbl1:** DISCOVER INOCA registry inclusion criteria.

Potential subjects must meet all of the following criteria to be eligible for inclusion in the study:
**General inclusion criteria:** • The patient is a male or nonpregnant female ≥18 y of age • The patient has suspected ischemic heart disease and is referred to undergo clinically indicated invasive coronary angiography • The patient has no obstructive coronary artery disease (CAD) as defined by (1) angiographically normal coronary arteries OR (2) nonobstructive CAD with angiographic stenosis <50%, or ≥50 but <70% with FFR ≥0.81 or RFR ≥0.90 • The patient is willing to comply with specified follow-up evaluations. The patient or legally authorized representative has been informed of the nature of the study, agrees to its provisions, and has been provided written informed consent approved by the appropriate institutional review board or ethics committee

CAD, coronary artery disease; FFR, fractional flow reserve; RFR, resting full cycle ratio.

**Table 2 tbl2:** DISCOVER INOCA registry exclusion criteria.

Potential subjects will be excluded if any of the following conditions apply:
**General Exclusion Criteria** 1. Pregnant or nursing patients 2. Any myocardial infarction at index presentation or within 90 d prior to enrollment, defined as any electrocardiogram diagnostic for myocardial infarction OR elevation in serum troponin greater than the upper limit of the site-defined reference range 3. Known LVEF <50% or cardiogenic shock requiring pressors or mechanical circulatory assistance (eg, intra-aortic balloon pump, left ventricular assist device, other temporary cardiac support blood pump) 4. Renal insufficiency, defined as estimated glomerular filtration rate (eGFR) <30 mL/min/1.73 m^2^ (by the Modification of Diet in Renal Disease equation) or dialysis at the time of screening 5. Prior percutaneous coronary intervention 6. Planned percutaneous coronary intervention (PCI) 7. Prior coronary artery bypass graft surgery 8. Prior ST-elevation myocardial infarction 9. History of hypertrophic cardiomyopathy 10. History of infiltrative heart disease (eg, cardiac amyloidosis) 11. New York Heart Association Class IV congestive heart failure 12. Severe mitral regurgitation 13. Severe aortic stenosis 14. Severe pulmonary hypertension (mean pulmonary artery pressure ≥35 mm Hg or echocardiographic right ventricular systolic pressure ≥60 mm Hg) 15. Known history of unrepaired or repaired congenital heart disease 16. Past or pending heart transplant, or on the waiting list for organ transplant 17. Known other medical illness or known history of substance abuse that may cause noncompliance with the protocol, or is associated with a life expectancy of less than 1 year 18. Current or planned participation in a study of an investigational therapy
**Angiographic Exclusion Criteria** 1. Angiographic stenosis in any major epicardial vessel ≥70% by visual estimate 2. Angiographic stenosis in any major epicardial vessel ≥50% and <70% by visual estimate with FFR ≤0.80 or RFR ≤0.89

eGFR, estimated glomerular filtration rate; FFR, fractional flow reserve; LVEF, left ventricular ejection fraction; NYHA, New York Heart Association; PCI, percutaneous coronary intervention; RFR, resting full cycle ratio.

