### Index procedure

Invasive CFT is intended to be performed as part of the standard of care evaluation for patients who present to the cardiac catheterization laboratory. After excluding the presence of obstructive CAD, the purpose of the procedure is to evaluate coronary vasoreactivity with acetylcholine provocation, physiology with thermodilution, identify myocardial bridging, and describe the burden of atherosclerosis by intravascular imaging (the DISCOVER INOCA index procedure protocol is included as a Supplemental Appendix).

The target vessel for physiologic analysis and intracoronary imaging will be the vessel in which physiologic assessment is clinically indicated or the left anterior descending artery. Coronary angiography will be performed using a standardized acquisition protocol. Angiograms will be acquired in at least 2 projections for each major artery or branch, and the treating physician will record an estimation of stenosis location and severity. The sequence of procedural elements including acetylcholine testing, wire-based testing, and intravascular imaging are at the discretion of the operator and will be recorded.

Coronary vasoreactivity testing will be performed with bolus injection or infusion of escalating doses of intracoronary acetylcholine via a guide catheter. Recommended doses for acetylcholine testing are listed in the Supplemental Appendix. Angiography will be performed after each dose with documentation of electrocardiogram changes and/or symptoms to evaluate for endothelial dysfunction, epicardial coronary vasospasm, and microvascular spasm (Figure 2).

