**Procedural End Points**
The following end points will be reported in-hospital (or within 48 h of the index procedure): • Reclassification from preprocedure diagnosis (including noncardiac chest pain) • Completion of the interventional diagnostic procedure without device-related serious adverse events or major angiographic complications • Frequency of major angiographic complications (device-related coronary artery dissection [greater than type C], slow or no flow, or perforation)

BARC, Bleeding Academic Research Consortium; CABG, coronary artery bypass grafting; CAD, coronary artery disease; EQ-5D-5L, EuroQol 5 Dimensions – 5 Levels; GAD, Generalized Anxiety Disorder; MACCE, major adverse cardiovascular and cerebrovascular events; MACE, major adverse cardiovascular events (composite of cardiovascular death, myocardial infarction, hospitalization for cardiovascular causes, or coronary revascularization); NeuroARC, Neurologic Academic Research Consortium; PHQ, Patient Health Questionnaire; PCI, percutaneous coronary intervention.

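### Enrollment is certified only after the coronary function tests, yet the MI and shock exclusions are not tied to status before the procedure, so patients harmed by testing can fall out of the safety end points

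*Protocol article*

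**What the plan says.** In the protocol article, the section on screening and eligibility fixes the moment of entry: "The point of enrollment is investigator certification at the completion of the index procedure cardiac catheterization that all eligibility criteria are met". The same section adds that participants stay in the registry whatever the procedure shows, normal physiology included.

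The index procedure is more than angiography. Study design lists what the core laboratories receive from it: "Index procedure angiographic data, physiologic assessments, and intracoronary imaging". The Index procedure section states that, once obstructive disease is excluded, "the purpose of the procedure is to evaluate coronary vasoreactivity with acetylcholine provocation, physiology with thermodilution", together with bridging and plaque assessment.

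Table 2 holds the exclusions that the investigator certifies at that point. Criterion 2 is "Any myocardial infarction at index presentation or within 90 d prior to enrollment, defined as any electrocardiogram diagnostic for myocardial infarction", or a troponin above the site's upper limit. Criterion 3 includes "cardiogenic shock requiring pressors or mechanical circulatory assistance", with no date attached. Criteria 5 and 6 exclude prior and planned PCI.

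Table 3 lists the procedural end points, reported during the hospital stay or within 48 hours. They include "Completion of the interventional diagnostic procedure without device-related serious adverse events or major angiographic complications" and the frequency of device-related dissection, slow or no flow, and perforation. The abstract's conclusions say that the registry will report "the safety of comprehensive invasive CFT, and the impact of testing on diagnoses and medical therapy".

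**The concern.** A safety rate needs a denominator fixed before the exposure. Here the exposure is the coronary function test, entry is certified after it, and two of the entry criteria can be failed through a complication of it. A patient who meets such a criterion during testing is never enrolled, so the event leaves the numerator and the patient leaves the denominator.

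At stake is the credibility of the completion and complication figures for CFT, which the article names among its outputs. Any such loss works in one direction, toward a safer-looking test. A later analysis cannot repair it, because the missing patients are not in the database.

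**Working it through.** **Step 1. Order of events, from the text.**
1. Consent, baseline questionnaires and preprocedure medications come before the procedure.
2. Angiography excludes obstructive CAD, with FFR or RFR where a stenosis is intermediate.
3. Acetylcholine testing, wire-based physiology and imaging follow, in an order left to the operator.
4. The catheterization is completed and the investigator certifies eligibility. This is enrollment.
5. Procedural end points are collected in hospital or up to 48 hours.

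**Step 2. Apply the exclusions at step 4 to an event at step 3.**
- *MI.* The window closes at enrollment, so an MI at step 3 lies inside it. A diagnostic electrocardiogram or any troponin above the limit is enough, and procedural events are not exempted.
- *Shock.* There is no time anchor. Certified at step 4, shock at step 3 can be read as meeting the criterion.
- *PCI.* Bail-out PCI at step 3 could be read as prior PCI at step 4.
- *Contrast.* The renal criterion is dated to screening. The table can anchor a criterion before the procedure, but does not do so for MI or shock.
- *Aborted test.* No criterion in Tables 1 or 2 requires a completed CFT. Loss here would come only from how sites read completion of the procedure.

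**Step 3. Does a stated rule recover these patients?** The retention rule protects people already enrolled and concerns findings, not complications. Adjudication of an event's relation to the procedure cannot reach someone who was never enrolled.

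**Step 4. Size, under assumptions.** The article gives no complication rate, no incompletion rate and no share of affected patients left uncertified, so there is no plan figure to reproduce. Let *c* be the true rate among tests started and *s* the share of affected patients not certified.

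Observed rate among enrolled = c(1 − s) / (1 − cs)

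| Assumed c | s = 0 | s = 50% | s = 100% |
|---|---|---|---|
| 1% | 1.0% | 0.005/0.995 = 0.5% | 0% |
| 2% | 2.0% | 0.010/0.990 = 1.0% | 0% |
| 5% | 5.0% | 0.025/0.975 = 2.6% | 0% |

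At c = 2%, s = 25% gives 0.015/0.995 = 1.5% and s = 75% gives 0.005/0.985 = 0.5%. Patients lost per 500 enrolled are 500/(1 − cs) − 500, which is 5.1 at s = 50% and 10.2 at s = 100%. In that extreme, 0/500 has an exact 95% interval of 0 to 0.74%, which excludes the assumed true 2%.

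For completion, with *i* the true rate of failing that end point, observed completion = (1 − i)/(1 − is). With i = 10% and s = 50% it is 0.90/0.95 = 94.7% against a true 90%. With i = 5% and s = 50% it is 0.95/0.975 = 97.4% against 95%.

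**The case against.** The best reply is that the MI and shock criteria are meant as history and presenting status. Criterion 2 opens with the index presentation, and criterion 3 sits beside a known low ejection fraction. That is probably the intention. It is not what the MI wording says, because the window closes at an enrollment that comes after the tests. Sites certify against the wording.

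Late certification also has a reason. Eligibility can depend on FFR, which is recorded in the same hyperemic run as CFR and IMR, so a point after FFR and before every study test does not always exist. This stands, and it is why the enrollment point should stay where it is.

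Other objections limit the reach of the point, and they also stand. A reader might infer any of the following, but the document does not support them:
- *Completion tends to 100% by construction.* No criterion demands a completed CFT, and an aborted test can still end in a completed catheterization and be certified.
- *All procedural end points precede enrollment.* The reporting window extends to 48 hours, so events after certification are counted.
- *Every major complication leads to exclusion.* Dissection, slow or no flow, and perforation are not exclusions in themselves. The patient would also need an MI, shock or PCI before certification.
- *Phenotype prevalence is selected on the test result.* No criterion lets an investigator withhold certification because of a phenotype, and the retention rule points the other way.
- *The preprocedure diagnosis is not recorded.* The article is condensed and its supplement is not shown, so silence proves nothing.

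Finally, the affected end points are secondary and descriptive, and no effect on the primary long-term end point has been shown.

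**Conclusion.** The point holds in a limited form. As written, the late enrollment point and the exclusions interact so that a patient with an MI, and on a literal reading shock, during testing and before certification becomes ineligible because of the harm that the registry intends to report. An aborted test may also go uncertified at a site's discretion. Any resulting bias makes CFT look safer.

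The size is unknown. The halving of an assumed 1% to 5% complication rate rests on the further assumption that half of the affected patients are not certified. If sites already read the exclusions as status before the procedure and certify everyone they test, there is no bias. The conclusion also assumes that the full protocol, which is not shown, repeats the article's enrollment and exclusion wording. Because the enrollment point and the MI window are both stated in the article, this is a fault in what is fixed and not a detail left to the analysis plan.

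**What to change.** 1. State that the MI and shock exclusions refer to status before the start of the index procedure. Do the same for the PCI exclusions if bail-out PCI could trigger them.
2. Define the denominator for completion and complications as all consented, otherwise eligible patients in whom any study test element was started.
3. Report patients in whom testing was started but who were not certified, with reasons. Include a retrospective check of site logs covering the patients screened so far; the article reports 100 enrolled.

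The enrollment point itself can remain. The baseline questionnaires are required before the procedure, so candidates are identifiable in advance and the wider denominator is feasible.

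The cost is a wording change, a data item recording when testing began, and a short log review. The downside is a few incomplete records and slightly less favourable completion and complication rates.

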**Figure 1 fig1:**
[figure not shown]
**DISCOVER INOCA registry patient flow diagram.** Patients who meet all inclusion and no exclusion criteria will be eligible for enrollment. CFR, coronary flow reserve; FFR, fractional flow reserve; IMR, index of microcirculatory resistance; RFR, resting wave-free ratio.

### Index procedure

Invasive CFT is intended to be performed as part of the standard of care evaluation for patients who present to the cardiac catheterization laboratory. After excluding the presence of obstructive CAD, the purpose of the procedure is to evaluate coronary vasoreactivity with acetylcholine provocation, physiology with thermodilution, identify myocardial bridging, and describe the burden of atherosclerosis by intravascular imaging (the DISCOVER INOCA index procedure protocol is included as a Supplemental Appendix).

The target vessel for physiologic analysis and intracoronary imaging will be the vessel in which physiologic assessment is clinically indicated or the left anterior descending artery. Coronary angiography will be performed using a standardized acquisition protocol. Angiograms will be acquired in at least 2 projections for each major artery or branch, and the treating physician will record an estimation of stenosis location and severity. The sequence of procedural elements including acetylcholine testing, wire-based testing, and intravascular imaging are at the discretion of the operator and will be recorded.

Coronary vasoreactivity testing will be performed with bolus injection or infusion of escalating doses of intracoronary acetylcholine via a guide catheter. Recommended doses for acetylcholine testing are listed in the Supplemental Appendix. Angiography will be performed after each dose with documentation of electrocardiogram changes and/or symptoms to evaluate for endothelial dysfunction, epicardial coronary vasospasm, and microvascular spasm (Figure 2).

